## Assignment of interventions: blinding

### Who will be blinded {17a}

Due to the nature of the intervention, it is not possible for study participants or treating HMV teams to be blinded. The Research coordinator responsible for collecting self-reported outcome measures will be blinded to the allocation assignment. The data analyst will be blinded.

### Procedure for unblinding if necessary {17b}

The design is open label with only outcome assessors being blinded so unblinding will not occur.

## Data collection and management

### Plans for assessment and collection of outcomes {18a}

Study data will be managed (collected and stored) using Research Electronic Data Capture (REDCap), a secure web-based tool for building and managing databases. Patients and family caregivers can complete the study questionnaires over the telephone with a research coordinator (who will input data in the REDCap), or via an electronic link sent via email through REDCap.

The study PI (RA) trained the assessors on the study procedures and tools. In addition, database development and management are being performed in partnership with the Ontario Child Health Support Unit (OCHSU). Data quality routine checks is being performed quarterly by OCHSU and there are standing meetings between the study team and OCHSU to review data quality issues, data check results, and potential data completion issues. In addition, a weekly report is generated by OCHSU for the research team regarding any data completeness/quality issues. Please see Item 12: Outcomes including Table 4 for a description of all the study instruments being used along with their reliability and validity. Data collection forms are available upon request from the study PI (RA).

### Plans to promote participant retention and complete follow-up {18b}

We will provide a CAN$25 voucher for all participants in lieu of their time and an additional $30 voucher for the subset of participants completing qualitative interviews. To promote study retention and increase engagement, in the intervention arm, the unblinded research coordinator will send a weekly message or “tip of the month” through the aTouchAway app. Messages will serve as reminders, and also be clinically relevant to the care of individuals using HMV.

### Data management {19}

All data entry will be done electronically. The research coordinator (MA) will enter data into the database for screening and randomization purposes. Study participants can enter the information directly into REDcap or this will be done by study personnel on their behalf over the telephone. After each data entry timepoint, study personnel reviews the data forms for completion. The OCHSU will develop weekly enrollment and quarterly data quality reports.

### Confidentiality {27}

A REDCap study database will be developed and maintained by the Ontario Child Health and Support Unit (OCHSU), the trial data management center. Participants will be identified in the database by a unique study ID number. Case report forms will also be linked by this ID. An external user interface will be created on REDCap for participants who opt to complete the surveys online. A separate secure list of participant names and contact information will be maintained in an encrypted Microsoft Excel spreadsheet. All study-related electronic data files will be password-protected and reside on the study lead hospital server. Only research team members will have access to the server study file location via password-protected computers.

#### Privacy considerations

aTouchAway™: operates in accordance with Ontario’s Personal Health Information Protection Act (PHIPA) policy. aTouchAway™ is password protected. Data is stored exclusively in a Canadian cloud with no trans-border data transmission. To prevent unauthorized access, maintain data accuracy, and ensure the correct use of information, Aetonix has put in place appropriate physical, electronic, and administrative procedures to safeguard and secure information. We will adhere to all of ICES’ privacy policies and procedures and the privacy best practices endorsed by CIHR (www.cihr irsc.gc.ca/e/290702.html#Summary). All non-ICES study data will be securely stored on OCSHU servers throughout the duration of the study and for up to 10 years after study completion. Anonymized trial data will be available upon completion of the study upon request to enable international prospective meta-analysis.

### Plans for collection, laboratory evaluation, and storage of biological specimens for genetic or molecular analysis in this trial/future use {33}

Please see {26b}; there will be no biological specimens collected.

## Statistical methods

### Statistical methods for primary and secondary outcomes {20a}

The number of ED visits will be analyzed using Poisson or negative binomial regression. Pearlin Mastery Scale scores at 12 months will be analyzed using linear or robust regression models depending on the distribution of the data and adjusting for baseline Pearlin score. Both analyses will adjust for the for the stratified clinical site. We will conduct a secondary analysis of the primary outcome, ED visits, adjusting for a priori chosen clinically important covariates: age, sex, and clinical site; and stratified by pediatric, adult ALS, and adult non-ALS and ventilation type (invasive or non-invasive ventilation). Analysis of secondary outcomes, viewed as exploratory in nature, will vary depending on the outcome: count data (i.e., number of hospitalizations) will be compared with Poisson or negative binomial regression as appropriate; hospital free survival via Kaplan- Meier curves and Cox proportional hazards; time to ED admission and hospitalization using Fine and Gray models to account for competing risk of death; continuous repeated measures outcomes (EQ-5D-3L/5D-Y, FECC, ZBI, and CCMT) using linear mixed effects models.

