## Assignment of interventions: allocation

### Sequence generation {16a}

Participants will be randomized to the intervention or usual care arms using a centralized randomization schedule through the Ontario Child Health Support Unit (OCHSU). Randomization will be stratified per site. Randomly permuted blocks of size 6 will be used to ensure that the two groups have similar size throughout the trial for each site as well as for the trial overall. We will use a 1:1 allocation ratio stratified by pediatric, adult amyotrophic lateral sclerosis (ALS) patients, adult non-ALS patients, and type of ventilation (invasive or non-invasive).

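### Of the three randomisation factors, only site enters the co-primary models; ALS status and ventilation type should be added as main effects

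*Protocol article*

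**What the plan says.** The section Sequence generation {16a} names three factors. The first is site: "Randomization will be stratified per site". The other two come with the allocation ratio: "1:1 allocation ratio stratified by pediatric, adult amyotrophic lateral sclerosis (ALS) patients, adult non-ALS patients, and type of ventilation (invasive or non-invasive". On blocking it says: "Randomly permuted blocks of size 6 will be used".

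The section Statistical methods for primary and secondary outcomes {20a} fixes the adjustment for the two co-primary outcomes, ED visits and caregiver Pearlin score: "Both analyses will adjust for the for the stratified clinical site". The Pearlin score is to be analysed with "linear or robust regression models depending on the distribution of the data and adjusting for baseline Pearlin score".

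The other two factors return only in an additional analysis of one outcome: "We will conduct a secondary analysis of the primary outcome, ED visits, adjusting for a priori chosen clinically important covariates: age, sex, and clinical site", which is also "stratified by pediatric, adult ALS, and adult non-ALS and ventilation type (invasive or non-invasive ventilation". No counterpart is stated for Pearlin.

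**The concern.** A model that leaves out a factor used to stratify randomisation does not reflect how the groups were formed. Stratification makes the arms alike on the factor, which reduces the true variability of the treatment estimate. The model receives no credit for this: variation due to the factor stays in the residual variance (Pearlin) or the dispersion (ED visits). If the factor predicts outcome, the reported standard error is too large, the interval too wide and the test conservative.

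This is not a detail left to an analysis plan. Section {20a} states the adjustment for both co-primary outcomes and accepts the principle by including one stratification factor. ED visits are the outcome at stake, because that outcome drives the sample size and has little power to spare.

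**Working it through.** **1. Which factors are missing.** Study setting {9} lists 4 adult and 4 pediatric centres as separate sites.

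| Randomisation factor | In co-primary models? |
|---|---|
| Site (8) | Yes |
| Pediatric vs adult | Yes, through site |
| ALS vs non-ALS among adults | No |
| Invasive vs non-invasive | No |

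If the factors are fully crossed, there are 4 × 2 + 4 × 4 = 24 strata. Adding the two missing factors as main effects uses 2 degrees of freedom.

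**2. The plan's own figures (Sample size {14}).**

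*Pearlin.* Inputs: difference 2.95, SD 4.5, power 90%, two-sided 5% (sidedness assumed). n per group = 2 × (1.960 + 1.282)² × (4.5/2.95)² ≈ 49. The t-test gives 90.1% power at 50 per group, so the stated 50 reproduces.

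*ED visits.* Inputs: 50% with any visit, mean 2.6 among them, so 0.5 × 2.6 = 1.3 per year; reduced rate 0.91; 200 per group. Negative binomial shape k from (1 + 1.3/k)^(−k) = 0.5 gives k = 0.603. Then

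- Var(log RR) = (1/1.3 + 1/0.91 + 2/0.603)/200 = (0.769 + 1.099 + 3.315)/200 = 0.0259, SE 0.161
- Power = Φ(|ln 0.70|/0.161 − 1.960) = Φ(0.256) = 60.1%

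Under this formula, 80% power needs 320 per group, so the stated 200 does not reproduce. That is a separate and larger matter. Here 60.1% serves only as the starting point.

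**3. ED gain from adding the two factors.** The documents do not say how strongly ALS status or ventilation type predicts ED visits. Assume they explain a share s of the overdispersion, and replace 2/k by (1 − s) × 2/k:

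| s | Power at 200 per group | n per group for 80% |
|---|---|---|
| 0 | 60.1% | 320 |
| 5% | 61.5% | 310 |
| 10% | 62.9% | 300 |
| 20% | 66.0% | 279 |
| 30% | 69.3% | 259 |

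The gain runs from 0 to 69.3 − 60.1 = 9.2 points. This slightly overstates it, because stratification has already reduced the estimate's true spread. At s = 30%, if that spread were as small as under adjustment (SE 0.145), the site-only test would have power Φ((0.3567 − 1.960 × 0.1610)/0.1447) = Φ(0.284) ≈ 61.2%, and the gain would be about 8 points.

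**4. ED simulation.** 400 patients, 8 sites, stratified blocks of 6, treatment rate ratio 0.70, negative binomial model without and with the two factors:

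| Assumed rate ratio per factor | Model SE, without / with | Power, without / with |
|---|---|---|
| 1.0 | 0.160 / 0.160 | 59% / 59% |
| 1.5 | 0.160 / 0.158 | 59% / 59% |
| 2.0 | 0.161 / 0.155 | 58% / 61% |

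**5. Mechanism, in a linear-model simulation.** Effects of the two factors are in residual SDs; the treatment effect for power is 0.28 SD.

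| Effect of each factor | Model SE, without / with | Type I error without | Power without |
|---|---|---|---|
| 0 | 0.100 / 0.100 | 5.6% | 79% |
| 0.3 | 0.101 / 0.100 | 4.7% | 78% |
| 0.6 | 0.105 / 0.100 | 4.2% | 76% |
| 1.0 | 0.114 / 0.100 | 3.0% | 71% |

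With the factors included, type I error is about 5% and power 78–79% throughout. At effects of 1.0 SD the true spread of the estimate hardly differs (0.103 without, 0.102 with). The overstated standard error, not a worse estimate, causes the lost power.

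**6. Pearlin at 200 per group.** 2.95/(4.5 × √(2/200)) = 6.56 standard errors, so power is above 99.9% with or without the factors.

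**The case against.** The strongest reply is that nothing here is shown to cost anything. The prognostic strength of both factors is unknown, the range starts at nil, and at a rate ratio of 1.5 per factor the ED simulation shows no power difference. The resulting test is conservative, not invalid, and blocking limits chance imbalance. The Pearlin model already contains a prognostic covariate, the baseline score, and has ample power. The two factors are also not ignored, since a secondary ED analysis uses them. All of this stands. It limits the size of the point but does not explain why one stratification factor is included and two are not.

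Three stronger readings are tempting and unsupported:

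- A reader might infer that both models adjust for nothing but site. That is true only among the stratification factors.
- A reader might infer that the omission certainly wastes precision, and convert squared ratios of model standard errors into a number of patients lost. The documents give no prognostic strength, and under stratified randomisation the estimate's true spread barely changes, so that conversion misleads.
- A reader might infer that the omission explains the ED power shortfall. Even at 30% explained overdispersion, power stays at 69.3%.

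**Conclusion.** The mismatch is real and specific: ALS status among adults and ventilation type are randomisation factors absent from both co-primary models. If they are prognostic, the reported standard error is too large and the test conservative; the treatment comparison remains valid. For ED visits the power gain from adding them runs from nil to about 9 points. This rests on a two-sided 5% test, 200 per group, k = 0.603 from the stated 50% with any visit, and an assumed share of overdispersion explained between 0 and 30%. For Pearlin the power gain is immaterial, and the reasons to act are consistency with the design and correct interval width. This is a free improvement, not a flaw that threatens the result.

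**What to change.** In section {20a}, state that both co-primary models include site, ALS status (adult ALS vs not) and ventilation type (invasive vs non-invasive) as main effects, with baseline score retained for Pearlin.

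Keep any treatment-by-stratum interaction analysis separate from the primary model. With interactions in the primary model, the treatment coefficient would become the effect in a reference stratum instead of the overall effect, and more than two degrees of freedom would be used.

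The cost is one sentence and two degrees of freedom. Both variables are already known at randomisation, so no new data are needed. The change should be made before the analyst sees outcomes by arm. It does not resolve the ED sample-size question, which needs its own answer.

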### Interim analysis {21b}

Interim analyses were not deemed necessary given the low-risk nature of the TtLIVE intervention.

### Methods for additional analyses (e.g., subgroup analyses) {20b}

#### Cost-utility analysis

We will conduct a cost-utility analysis (CUA) to determine the incremental costs (or cost-savings) of the TtLIVE intervention versus usual care for improving quality-adjusted life years (QALYs). A health system and societal approach will be used with a 12-month time horizon. Direct health care costs, including costs of the intervention and health services used during the study period, will be collected from the AHCR-hybrid and by linkage with administrative databases. Costs associated with health care usage as determined in the health administrative data will be used to determine direct health care costs. Direct patient costs will include out-of-pocket expenses attributable to obtaining health care for their HMV. Indirect patient costs will include productivity losses and lost leisure time. Utility will be measured with the EQ-5D-3L and EQ-5D-Y. Cost-effectiveness will be expressed as the incremental cost-effectiveness ratio (ICER), calculated by dividing incremental costs between treatment and usual care arms by the incremental change in QALYs from baseline and 12 months. Costs will be reported in 2023 Can$. Extensive one-way deterministic sensitivity analyses will be performed to evaluate the robustness of the results and to evaluate uncertainty in any assumptions. Probabilistic sensitivity analysis using Monte Carlo simulation will be used to further evaluate uncertainty and establish a point estimate and 95% confidence interval around the ICER.

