### Sample size {14}

To determine our sample size we used simulations and data from our previous study of VAIs using Ontario health administrative data [2]. We simulated data based on a negative binomial distribution assuming 50% of VAIs visit the ED and had a mean number of 2.6 visits, for an overall yearly incidence rate of 1.3 ED visits. We need 200 participants/ study group to detect a 30% drop-in yearly incidence rate to of 0.91 at 12 months with *α* = 5% and power 80%. Given an estimated attrition rate of 10%, we will recruit a total of 440 participants. For our co-primary outcome, assuming a minimum clinically important difference in the Pearlin Mastery Scale score of 2.95, standard deviation of 4.5, power of 90%, and alpha = 5%, we would require a sample size of 50 study participants in each group for a total of 100 participants [38, 39]. Therefore, with our planned sample size of 440 participants, we are powered for our co-primary outcomes of ED visits and family caregiver reported Pearlin Mastery Scale score.

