## Discussion

In this study, we will investigate the impact of the TtLIVE intervention delivered through the e-platform aTouchAway™ compared to usual care on healthcare utilization, impact on the patient, family, healthcare costs, and healthcare providers on individuals newly transitioning to HMV. A virtual care platform that offers a comprehensive bundle of virtual care solutions that is sophisticated enough for the complex care demands of the HMV population was not previously in existence. Despite the substantial burden on acute and community healthcare resources, rising population prevalence, profound impact on VAIs and their family caregivers in terms of quality of life and caregiver burden, VAIs and their multiple care transitions remain sub-optimally managed. VAIs are particularly vulnerable due to the new and complicated technology, significant medical complexity, reliance on family caregivers, limited timely access to HMV specialists, and the need to access care across multiple health sectors and disciplines. Therefore, optimization of HMV transitions is imperative. We hypothesize that this virtual transition intervention will reduce emergent healthcare utilization, improve the experience of care, reduce caregiver burden, decrease costs, and enable more efficient use of healthcare provider time.

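### The cost-utility uncertainty is to be summarised as a 95% confidence interval around the ICER, which may be unreadable for a decision if costs fall or the QALY difference is not clearly above zero

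*Protocol article*

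**What the plan says.** The Cost-utility analysis section, under Methods for additional analyses {20b} of the protocol article, sets out "to determine the incremental costs (or cost-savings) of the TtLIVE intervention versus usual care". On perspective and horizon it says: "A health system and societal approach will be used with a 12-month time horizon". The result is an ICER: the between-arm difference in cost divided by "the incremental change in QALYs from baseline and 12 months". One-way deterministic sensitivity analyses are planned. A probabilistic sensitivity analysis by Monte Carlo simulation will then "establish a point estimate and 95% confidence interval around the ICER".

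The Discussion gives the expected direction of cost. The intervention is hypothesised to "decrease costs, and enable more efficient use of healthcare provider time".

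The sample size section rests on ED visits and the Pearlin Mastery Scale only: "We need 200 participants/ study group" for ED visits, and "Given an estimated attrition rate of 10%, we will recruit a total of 440 participants". The article gives no expected QALY difference, QALY SD, cost SD or willingness-to-pay threshold.

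**The concern.** An ICER is a ratio, and its value alone does not identify the result behind it. A cheaper, better result (dominant) and a dearer, worse one (dominated) both have a negative ICER. A dearer, better result and a cheaper, worse one both have a positive ICER. If the simulated draws fall in more than one of these quadrants, ranking them by ICER mixes opposite conclusions. If the QALY difference is not clearly away from zero, a ratio interval that keeps its coverage can be unbounded.

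Two features of the plan make this a realistic possibility. It allows for falling costs and hopes for them, so negative ratios would be a sign of success. And nothing in the sample size secures precision for QALYs over a 12-month horizon. Determining cost-effectiveness is a stated aim (Discussion paragraph of the Abstract; secondary objective 8 in Objectives {7}), so the summary chosen for it should be one that can be read whatever the data show.

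**Working it through.** The article states no figure for this analysis, so there is nothing to reproduce. The check asks when an interval around the ICER can be read.

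**1. The sign problem, by arithmetic alone (values chosen for illustration)**

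| Cost difference | QALY difference | ICER per QALY | Meaning |
|---|---|---|---|
| −$2,000 | +0.02 | −$100,000 | dominant |
| −$2,000 | +0.10 | −$20,000 | dominant, and better |
| +$2,000 | −0.02 | −$100,000 | dominated |
| +$2,000 | +0.02 | +$100,000 | dearer, better |
| −$2,000 | −0.02 | +$100,000 | cheaper, worse |

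Rows 1 and 3 have the same ICER and opposite meanings, as do rows 4 and 5. Row 2 is better than row 1 but has the less negative ICER. None of this needs a variance, or a QALY difference close to zero.

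**2. Chance that the simulated QALY difference is negative**

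- From the article: 440 recruited, 10% attrition, 1:1 allocation, so 440 × 0.90 / 2 = 198 per arm.
- Assumed: QALY SD 0.15 to 0.30; true QALY gain 0.02, 0.05 or 0.10.
- SE = SD × √(2/198) = SD × 0.1005. P(negative) = Φ(−gain/SE).
- A 95% Fieller interval for a ratio is bounded only when the denominator differs from zero at the two-sided 5% level. The chance that it is bounded is therefore the power of that test.

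| SD | SE | P(negative), gain 0.02 | P(bounded), gain 0.02 | P(bounded), gain 0.05 | P(bounded), gain 0.10 |
|---|---|---|---|---|---|
| 0.15 | 0.0151 | 9% | 26% | 91% | 100% |
| 0.20 | 0.0201 | 16% | 17% | 70% | 100% |
| 0.25 | 0.0251 | 21% | 13% | 51% | 98% |
| 0.30 | 0.0302 | 25% | 10% | 38% | 91% |

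At a gain of 0.10, P(negative) is at most 0.05% across these SDs.

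**3. A worked case, every input assumed**

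QALY SD 0.25, gain 0.02, cost SD $20,000, true saving $500, costs and QALYs uncorrelated, threshold $50,000 per QALY, 198 per arm.

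- Simulated draws fall in all four quadrants: about 32% dearer and better, 47% dominant, 9% dominated, 13% cheaper and worse.
- A simple percentile interval for the ICER runs from roughly −$0.78 million to +$0.74 million per QALY.
- Net monetary benefit = 50,000 × QALY difference − cost difference. Its mean is 50,000 × 0.02 + 500 = $1,500. Its SE is √[(50,000 × 0.0251)² + (20,000 × 0.1005)²] ≈ $2,370. The 95% interval is 1,500 ± 1.96 × 2,370, or about −$3,146 to $6,146.

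**4. When the QALY gain is clear but costs may fall**

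Now assume a gain of 0.10, SD 0.20, a saving of $2,000, and the same cost SD. Virtually no draw has a negative QALY difference. About 84% are dominant and 16% dearer and better. The percentile interval is about −$67,500 to $20,200. It is bounded, but its negative part is not ordered from better to worse, as rows 1 and 2 of the first table show.

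**The case against.** - **The documents do not say that the QALY difference will be small.** That is correct. Every variance and effect in the working is assumed, and at a gain of about 0.10 the straddling of zero is close to gone. The point is conditional. The sign problem does not need a small gain, only falling costs, which the plan itself anticipates.
- **The article does not say how the interval will be built.** This also stands. The percentile interval above is an illustrative choice. But changing the construction does not rescue the summary: a percentile interval mixes quadrants, and a Fieller interval may be unbounded.
- **A condensed article may leave the plane, acceptability curve and net benefit to the full plan.** Agreed; their absence is not the finding. The finding is the summary that the article does name.
- **Net benefit also spans zero in the worked case.** It does, so the decision stays uncertain. The gain is that the uncertainty is finite and has a consistent direction.
- **A reader might infer that the ICER denominator is wrong**, because "by the incremental change in QALYs from baseline and 12 months" could be taken as a two-point change in utility. The documents do not support that. Secondary objective 8 speaks of cost per QALY gained at 12 months, EQ-5D is collected at baseline, 6 and 12 months, and the phrase reads naturally as loose wording for QALYs accrued over the year. How utilities become QALYs is detail that an article may leave to the full plan. Clearer wording would help, but this is not part of the point.

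**Conclusion.** The concern holds in a limited form. The article commits to a 95% confidence interval around the ICER as its only named probabilistic summary, in a plan that allows for cost-savings and is not sized on QALYs. If costs fall, or the QALY difference is not clearly above zero, that interval will be unbounded or cannot be read for a decision.

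A reader might go further and conclude that the interval is bound to be uninterpretable. The documents do not support that: they give no QALY or cost figures, and with a clear QALY gain and a clear cost increase an ICER interval is usable. The 9% to 25% of negative draws rests wholly on an assumed gain of 0.02 and SD of 0.15 to 0.30; the dollar intervals rest in addition on the assumed costs, zero correlation and, for net benefit, the threshold.

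The consequence is confined to a secondary analysis. The co-primary results, sample size and alpha do not change. The correction is still worth making, because cost-effectiveness is a stated aim and the better summary costs almost nothing.

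**What to change.** In {20b}, replace the commitment to an ICER interval with the following, all from the same joint simulations of costs and QALYs:

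- Report incremental net monetary benefit (threshold × QALY difference − cost difference) with a 95% interval at stated thresholds, for both the health system and the societal perspective.
- Show the draws on the cost-effectiveness plane or as an acceptability curve.
- Give the ICER as a point estimate. Add an interval only if essentially all draws lie in the single quadrant with a QALY gain and a cost increase; otherwise describe the result in words, such as dominant, with the share of draws in each quadrant.

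This needs no new data. The cost is a few lines of text and the need to state the thresholds, preferably before the data are analysed.
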